### Data collection

The majority of data will be obtained from the routine admission documentations and electronic patient record and recorded in an online password protected spreadsheet. The variables recorded will include:

1) Demographics: Age, gender, deprivation score/ Scottish Index Multiple Deprivation (SIMD) [14] score (1 to 5), ethnic origin.

2) Co-morbidities: Charlson co- morbidity index (number of co-morbidities < 5 or ≥ 5) [15].

3) Polypharmacy (> 5 regular medications).

4) Lifestyle: alcohol intake (unit per week), smoking status (currently, ex-smoker < 5 year, ex-smoker ≥ 5 years, never smoked), weight and Body Mass Index.

5) Place of residence: home and independent, home with carers, home with family support, sheltered housing, nursing home.

6) Indication for and type of surgery: as per NELA criteria [4].

7) Prognostic scores: NELA score.

8) ASA (American Society of Anaesthesiology) score [16].

Frailty markers (pre-operative):

1) Plasma samples obtained using 6ml lithium heparin tubes for ultra-high performance liquid chromatography mass spectrometry analysis (UHPLC-MS).

2) Sarcopenia on CT abdomen pelvis [17].

3) Malnutrition Universal Screening Tool (MUST) score.

4) Routine Abbreviated Mental Test (AMT) score.

5) Routine serum biochemistry and haematology: Hb, White cells, neutrophils, C- Reactive protein, Albumin.

6) Rockwood Clinical Frailty Scale (CFS; assessing the baseline frailty status 2 weeks before admission with scores from 1 to 9 as frailty increases). Score of ≥ 4 will be grouped as frail [8].

Follow up variables recorded are:

1) Day 1, day 7 or discharge day if before day 7, day 30 and day 90 blood samples.

2) Total hospital stay including critical care stay.

3) Place of residence post discharge following emergency laparotomy.

4) Day 30 readmission.

5) Day 30 morbidity/ complications (according Clavien-Dindo classification Surgical Complications) [18].

6) Day 30 and day 90 mortality.

7) EQ-5D-5L on day 30 and 90.

8) Day 90 CFS.

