### Assessment of Sarcopenia

Participants of this study who underwent CT abdomen pelvis pre- operatively will be measured for sarcopenia [17]. The measurement of total cross-sectional area of psoas muscle (total psoas area, TPA) on L3 vertebra level will be performed using PACS (Picture Archiving and Communication System software). The area measured is standardised by measuring at the level where both L3 transverse processes were maximally in view on CT. The TPA is standardised for patient height using formula of TPA (mm^2^)/ height (m^2^) providing the total psoas index (TPI). The TPI will be stratified according to gender with sarcopenia being present in the lowest quartile [19].

Calculations of inter and intra- class correlation coefficients (ICCC) will be performed to ensure reliability of the measurement technique. The inter and intra ICCC will be calculated where the r^2^ value of > 0.8 indicates excellent correlation and ICCC value close to 1 indicates high similarity and high reliability.

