### Sample size

This is an exploratory study comparing different frailty markers in emergency laparotomy therefore no formal sample size calculations were performed. Historically, the centre where the participants are recruited from performed about 200 EmLAP per year. Based on the UK Observational Emergency Laparotomy and Frailty (ELF) study [5], 20% of older patients undergoing laparotomy had frailty pre- EmLAP. For this study, 20% of dropout/ loss to follow up/ withdrawal from study was anticipated [21] therefore a target total of 150 patients was established.

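### The only numeric benchmark for psoas reader reliability is r² > 0.8, which cannot show one reader measuring systematically higher or lower; the accompanying ICC has no stated form or minimum

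*Protocol article*

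**What the plan says.** All the text on this point is in the protocol article, section Assessment of Sarcopenia, unless noted.

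- Measurement: "The measurement of total cross-sectional area of psoas muscle (total psoas area, TPA) on L3 vertebra level will be performed using PACS". The area is divided by height squared to give the total psoas index (TPI).
- Purpose and statistic of the reliability check: "Calculations of inter and intra- class correlation coefficients (ICCC) will be performed to ensure reliability of the measurement technique".
- How the results are to be read: an r² "value of > 0.8 indicates excellent correlation and ICCC value close to 1 indicates high similarity and high reliability".
- Classification: "The TPI will be stratified according to gender with sarcopenia being present in the lowest quartile".
- Use: the section Data collection lists "Sarcopenia on CT abdomen pelvis" among the preoperative frailty markers that the study compares.

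The article does not state whether the ICC is for absolute agreement or consistency, how many readers there are, which reader's values are analysed, or whether the quartile is formed within the cohort or taken from the cited source.

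**The concern.** The check is meant to show that the measurement is reliable, so that it matters little who measured a scan or when. That is a question of agreement. r² answers a different question: whether two sets of readings lie on some straight line. If one reader draws the muscle border consistently further in, the points still lie on a line and r² does not move. A numeric benchmark placed on r² alone can therefore be met easily while two readers differ by a clinically visible amount.

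The second statistic does not clearly close the gap. Being near 1 is not a defined standard, and one common form of the ICC removes the reader mean before it compares the readings.

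The stake is the CT marker in the primary-aim comparison. TPI becomes sarcopenia through a quartile cut, so an undetected offset can, under some reading arrangements, move patients across the cut according to who measured them.

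**Working it through.** **Inputs from the article:** r² > 0.8; ICC near 1 with no cut-off; sarcopenia as the lowest gender-specific quartile of TPI.

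**Assumptions (the article gives no such figures):** true TPI normal with mean 1 and SD 0.25; independent reader error SD 0.04; reader 2's reading is k × (true value + error), with k = 1, 0.9 or 0.8 (no offset, 10% smaller, 20% smaller).

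**Step 1: what each statistic sees.** Reader 1's variance is 0.25² + 0.04² = 0.0641 (SD 0.2532). Reader 2's is k² × 0.0641. Their covariance is k × 0.0625.

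- r² = (k × 0.0625)² / (0.0641 × k² × 0.0641) = (0.0625/0.0641)² = 0.951. The offset k cancels.
- Consistency ICC = 2 × 0.0625k / [0.0641(1 + k²)].
- Absolute-agreement ICC = 2 × 0.0625k / [0.0641(1 + k²) + (1 − k)²].

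| Reader 2 | r² | Consistency ICC | Absolute-agreement ICC |
|---|---|---|---|
| no offset | 0.951 | 0.975 | 0.975 |
| 10% smaller | 0.951 | 0.1125/0.1160 = 0.970 | 0.1125/0.1260 = 0.893 |
| 20% smaller | 0.951 | 0.1000/0.1051 = 0.951 | 0.1000/0.1451 = 0.689 |

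The same holds just above the article's benchmark. With r² = 0.81 (r = 0.90) and a constant shift of b SD, r² stays at 0.81 and consistency ICC at 0.90. Absolute-agreement ICC is 1.8/(2 + b²): 0.90 at b = 0, 0.80 at b = 0.5, 0.60 at b = 1 and 0.42 at b = 1.5.

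**Step 2: does the offset reach sarcopenia status?** There are three possible arrangements.

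(a) *One reader measures every scan and quartiles are formed within the cohort by gender.* A uniform offset multiplies all values and the cut by the same k, so each patient stays on the same side. No classification changes.

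(b) *Two readers each measure a random half and the quartile is pooled.* The cut c solves ½Φ((c − 1)/0.2532) + ½Φ((c − k)/(0.2532k)) = 0.25. This gives c = 0.783 at k = 0.9 and c = 0.727 at k = 0.8. Misclassification against true quartile status is by simulation.

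| Offset | Sarcopenic, reader 1 | Sarcopenic, reader 2 | Misclassified |
|---|---|---|---|
| none | 25% | 25% | 4.0% |
| 10% | 19.6% | 30.4% | 6.1% |
| 20% | 14.1% | 35.9% | 11.0% |

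If all 150 patients had a usable CT, the extra misclassified patients would number about 150 × (0.061 − 0.040) ≈ 3 at a 10% offset and 150 × (0.110 − 0.040) ≈ 10 at 20%.

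(c) *A fixed cut is carried over, here reader 1's quartile: 1 − 0.6745 × 0.2532 = 0.829.* Reader 2 then places Φ((0.829 − 0.9)/0.2279) ≈ 38% below it at a 10% offset and Φ((0.829 − 0.8)/0.2025) ≈ 56% at 20%, instead of 25%.

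**The case against.** The strongest reply is that the article does not judge reliability by r². It names the ICC as the reliability calculation, describes r² only as showing correlation, which is what r² shows, and ties similarity and reliability to the ICC. The sentence is a guide to reading results and attaches no consequence to failing. The form of the ICC and its minimum are details that a condensed article may leave to the full protocol or the analysis plan.

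Much of this stands. A reader might infer that r² is the sole test of reliability; the text does not support that, because an ICC is planned beside it. The unstated ICC form and cut-off are not a finding in themselves. What remains is printed text: in a check whose declared purpose is reliability, the one number given is on a statistic that cannot detect reader bias.

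A reader might also infer that sarcopenia status will depend on who measured the scan, with 38% or 56% of patients below the cut. The documents do not support that either. Those shares need a fixed or carried-over cut, and the article gives no cut value. Planning an inter-reader coefficient implies at least two readers for the repeat readings, but one reader may supply every analysed value, and then arrangement (a) applies.

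Finally, no source in the article supports offsets of 10% or 20%. Sarcopenia is one of six listed markers in a study that calls itself exploratory. Both points limit the severity.

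**Conclusion.** The point holds in a narrow form and is minor. The benchmark r² > 0.8 is unsuitable as evidence of reader reliability, because it is unaffected by a constant or proportional reader offset of any size. The planned ICC repairs this only if it is the absolute-agreement form, and nothing shown fixes that.

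The effect on sarcopenia status is conditional. It is nil with one reader and within-cohort, gender-specific quartiles. With scans split equally and a pooled quartile, it is a gap of about 20% versus 30% sarcopenic by reader at a 10% offset (14% versus 36% at 20%), with misclassification of 6.1% (11.0%) against 4.0% without an offset. These sizes rest on the assumed 25% coefficient of variation, 4% reader error, normality and random allocation of scans to readers. The blindness of r² rests on none of them.

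**What to change.** In Assessment of Sarcopenia:

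1. Remove r² > 0.8 as a reliability criterion.
2. State a two-way random-effects, absolute-agreement, single-measure ICC for inter- and intra-reader readings, with its 95% confidence interval and a preset minimum (for example, lower limit above 0.8).
3. Report the Bland-Altman mean difference and limits of agreement alongside it. This is needed because a 10% offset still gives an absolute-agreement ICC of 0.89 under the assumptions above, which could pass such a minimum.
4. State how many readers there are and which reader's values are analysed. Use one reader's values for the whole cohort or, if readings are shared and an offset is found, correct for it before TPI enters the marker comparison.
5. State whether the quartile is formed within the cohort.

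The cost is a few sentences. The first three items use the repeat readings already planned. The reported reliability may look slightly less favourable, and having one reader measure every scan takes some reader time if that is not already the arrangement.

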### Management of blood samples

Blood samples will be obtained at 5 time points (preoperatively, postoperative day 1, 7 or discharge day if before day 7, day 30 and day 90) using 6mL lithium heparin vacutainers. The sample will be centrifuged to have plasma extracted and stored at -40 °C. These will then be sent on for ultra-high performance liquid chromatography mass spectrometry analysis (UHPLC-MS) in Strathclyde Institute of Pharmacy & Biomedical Sciences, University of Strathclyde for analysis.

### Ultra-high Performance Liquid Chromatography mass spectrometry analysis

A semi-targeted ultra-high performance liquid chromatography mass spectrometry-based metabolomics approach (UHPLC-MS) will be performed to determine metabolic signatures correlated to frailty status and surgical outcome. This will be performed on a Thermo Exploris 240 mass spectrometer coupled to a Thermo Vanquish binary liquid chromatography instrument. The applied method will contain a range of predefined targeted mass measurements (using product ion multiple reaction monitoring) related to a defined group of biochemically annotated metabolites already identified in previous research [13] which include 13-carboxy-alpha-tocotrienol, stearoylcarnitine, vaccenyl carnitine, urocortisol, 13-carboxy gamma-tocotrienol, hexacosonyl carnitine, formyl-N-acetyl-5-methoxykynurenamine, arginine, gamma-tocotrienol, linoleyl carnitine, arachidonic acid and prostaglandin G2. A range of other chemical classes will also be targeted that will cover aspects of dietary response and polypharmacy – determined by pre-operative information provided by the patient cohort.

### Assessment of postoperative quality of life

The EQ-5D-5L questionnaire is a validated measurement tool which evaluates 5 dimensions of quality of life including mobility, self-care, activity of daily living, pain/ discomfort and psychological status [20]. This questionnaire will be used to assess the participant’s quality of life at postoperative day 30 and 90.

### Sample size

This is an exploratory study comparing different frailty markers in emergency laparotomy therefore no formal sample size calculations were performed. Historically, the centre where the participants are recruited from performed about 200 EmLAP per year. Based on the UK Observational Emergency Laparotomy and Frailty (ELF) study [5], 20% of older patients undergoing laparotomy had frailty pre- EmLAP. For this study, 20% of dropout/ loss to follow up/ withdrawal from study was anticipated [21] therefore a target total of 150 patients was established.

### Statistical analysis

The categorical variables (demographics, co-morbidities, polypharmacy, ASA score) will be expressed as n and percentage (%) and continuous variables (age) as mean ± standard deviation. The frailty markers (score 1–9) will be compared between groups of frail (CFS ≥ 4) and non-frail (CFS ≤ 3). Categorical variables will be analysed using Chi-square or Fisher Exact test. All normally distributed continuous variables will be assessed with Student’s T-test or the ANOVA test and for the non- normal distribution variables, the rank based Kruskal- Wallis non-parametric test will be used to determine the statistical significance between the different groups.

The primary analysis of metabolomics data will involve a range of pre-processing normalisation procedures to help scale the differences in the magnitude of metabolite concentrations. Normalised features will then be compared for analytical reproducibility by using multivariate principal component analysis (PCA) to determine QC clustering and outlier identification. Further analysis of clinical frailty markers and between groups of frail and non-frail (defined by clinical frailty scale binning) using the Kruskal-Wallis t-test or Mann Whitney test and subsequently in a regression model and propensity score matching, adjusting for appropriate demographics and other baseline variables. A linear mixed model will also be used on the normalised data to study the changes of each metabolite over time to identify differences between frailty status, response post-surgery and polypharmacy interactions.

The association between frailty markers and mortality will be analysed using regression model and will be adjusted for confounding factors such as presence of sepsis and type of surgery. Sensitivity and specificity analyses will be performed using the Receiver Operating Characteristic curve (ROC). A p-value of < 0.05 is considered statistically significant.

Result from EQ-5D-5L questionnaire will be reported and analysed quantitatively (means and ranges of 5 domains) using the analysis tool (index value set calculator and analysis of observational descriptive systems data) provided by the EuroQol Office [22].

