## Background

Emergency laparotomy (EmLAP) is one of the commonest emergency operations performed in the United Kingdom with approximately 30,000 laparotomies performed annually in England and Wales [1]. Frail patients have been shown to have significantly poorer outcomes, especially in older adults (≥ 65 years) [2, 3]. According to the recent 8th patient report of National Emergency Laparotomy Audit (NELA), more than 22,000 patients underwent emergency laparotomy in a year and more than half (55.3%) of these patients were ≥ 65 years. The report found that risk of mortality doubled among frail patients undergoing EmLAP [4]. These findings were mirrored in the first multi-centred observational study, the Emergency Laparotomy Study (ELF study) [5]. Using the Rockwood Clinical Frailty Scale (CFS), the ELF study reported 20% of older adults had frailty pre-EmLAP. As frailty increased, independent of age, 30-day 90-day morality did too. Furthermore, the presence of frailty resulted in an increased level of dependence at discharge highlighting the significant and prolonged health demands of frailty.

Frailty is a clinical syndrome of increased vulnerability that results from ageing associated multi-system physiological decline [6]. Such a decline reduces the ability of the individual to cope with physiological stress such as surgery (surgical frailty) and negatively impact on their quality of life. Frailty can be identified using different questionnaires and assessments depending on what aspect of the syndrome is being looked at. This includes but not limited to muscle wasting (sarcopenia), malnutrition, cognition (memory, orientation and processing), physical function and capacity [7–10]. Most studies associate frailty with the older population, but frailty has also been shown to exist in younger individuals [11]. Moreover, there could be a time gap between biological changes and phenotypic manifestations of frailty (pre- frail) [12]. To date, there isn’t a frailty assessment tool that has been identified as the gold standard for assessing frailty in all clinical situations including emergency setting. Hence, an objective measurement of frailty is required to not only identify and modify frailty, but in understanding the biology of ageing that leads to a clinical diagnosis of frailty.

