One of the largest research studies on role of metabolomics in frailty [13] demonstrated how mass spectrometry can be used to understand changes in blood metabolism across frailty. Serum samples from 1200 people from within the English Longitudinal Study of Ageing (ELSA- www.elsa-project.ac.uk) were chemically profiled and mapped on to associated Rockwood Frailty Index calculations and altered levels of 12 metabolites were found to be dysregulated in those that were consider frail. These included 3 tocotrienols and 6 carnitines- metabolites known to be directly involved in energy metabolism, which was used to differentiate between frail and non-frail patients. These findings indicated that decreased energy production acts as a common pathway and a primary driver toward frailty which was reflected globally by frail individuals presenting symptoms of weakness, slowness, exhaustion and low activity. These results provided a platform for this study to establish a panel of novel frailty biomarkers in emergency laparotomy patients and correlate blood metabolites with changes in frailty due to EmLAP, postoperative morbidity and mortality.

No clinical chemical biomarkers for frailty currently exist in practice due to a lacking in the understanding of the biochemical aetiology of frailty. However, early detection of subclinical changes or deficits at the molecular level are essential in improving our understanding of the biology of frailty and ultimately improving patient outcomes, aiding in shared decision-making, precision medicine and development of new optimal postoperative EmLAP patient pathway.

The primary aim of this study is to compare preoperative frailty markers including establishing a novel blood-based biomarker panel that could identify frailty in EmLAP patients and their ability to predict 30 and 90-day mortality post-EmLAP. The secondary aim is to analyse the influence of perioperative frailty on 30-day morbidity and quality of life post-EmLAP.

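### CFS is tested as a marker between groups cut from CFS itself, and splitting it at 4 discards about half the information for the metabolite-frailty question

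*Protocol article*

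**What the plan says.** The Data collection section lists six pre-operative frailty markers. The sixth is CFS, described as "assessing the baseline frailty status 2 weeks before admission with scores from 1 to 9 as frailty increases". The same item sets the grouping rule: "Score of ≥ 4 will be grouped as frail".

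The Statistical analysis section then uses that rule twice.

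- For the markers: "The frailty markers (score 1–9) will be compared between groups of frail (CFS ≥ 4) and non-frail (CFS ≤ 3".
- For the further marker and metabolite analysis, the contrast is "between groups of frail and non-frail (defined by clinical frailty scale binning", first by rank tests and "subsequently in a regression model and propensity score matching, adjusting for appropriate demographics and other baseline variables".

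A later paragraph of the same section plans a regression of mortality on the frailty markers with confounder adjustment, followed by ROC analysis. Neither uses CFS groups as its stated yardstick.

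The Background section gives the primary aim in two parts, with death by day 30 and by day 90 as the outcome of the second part: "compare preoperative frailty markers including establishing a novel blood-based biomarker panel that could identify frailty in EmLAP patients and their ability to predict". On existing tools, the same section states that "there isn’t a frailty assessment tool that has been identified as the gold standard for assessing frailty in all clinical situations".

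**The concern.** CFS has three roles: it is a marker under test, it defines the groups in which markers are tested, and it is the standard against which metabolites are first judged. Three consequences follow.

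1. One planned comparison has its result fixed before any patient is recruited. If it is reported beside the other markers, CFS will look like a perfect discriminator and every other marker will look worse.
2. A frail versus non-frail contrast says how well a marker reproduces CFS. Since CFS is the reference, no marker can beat it there. A good result must not be read as evidence that the panel improves on CFS.
3. A score collected on nine levels is reduced to two for the metabolite question, in a cohort where one of the two groups is likely to be small.

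**Working it through.** **Inputs.** From the Sample size section: target 150, 20% anticipated loss, and 20% frailty (quoted for older patients). The article gives no formal size calculation ("This is an exploratory study comparing different frailty markers in emergency laparotomy therefore no formal sample size calculations were performed"), so there is no power figure to reproduce. Reading the loss as 150 × 0.80 = 120 evaluable patients is an assumption. At 20% frail this gives 0.20 × 120 = 24 frail and 96 non-frail.

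**Step 1: CFS against its own split.** Every frail patient scores higher than every non-frail patient, so the Mann-Whitney U takes its maximum.

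- U = 24 × 96 = 2304, so AUC = 2304/2304 = 1.0.
- Under the null, mean = 1152 and variance (no tie correction) = 24 × 96 × 121/12 = 23,232, so SD = 152.4.
- z = (2304 − 1152)/152.4 = 7.56, two-sided p ≈ 4e-14. Correcting for ties makes p smaller still.

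In 2,000 simulated samples of 120 with 20% expected frail, AUC was 1.000 every time and the largest p was 3e-9.

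**Step 2: is the metabolite contrast circular too?** In the same simulation a metabolite unrelated to CFS was declared different between the groups in 4.7% of samples, which is the nominal 5%. It is not circular.

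**Step 3: can that contrast show added value?** Two panels were simulated with the same association with CFS. One carried no information on death beyond CFS and the other carried strong extra information (400,000 patients each; CFS distribution, effects and mortality of 6–8% all assumed).

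| Panel | AUC for CFS ≥ 4 | AUC for death: CFS | AUC for death: CFS + panel |
|---|---|---|---|
| No extra information | 0.827 | 0.695 | 0.695 |
| Strong extra information | 0.827 | 0.683 | 0.773 |

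The frail/non-frail contrast cannot tell the two panels apart. The mortality analysis can.

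**Step 4: information lost by the split.** If CFS reflects a normal trait and a proportion p lies above the cut z, the split keeps φ(z)²/[p(1 − p)] of the information in the ungrouped trait.

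- p = 0.20: z = 0.842, φ = 0.280, so 0.0784/0.160 = 0.49.
- p = 0.11: z = 1.227, φ = 0.188, so 0.0353/0.0979 = 0.36. This is the low end if the 20% applies only to the 55.3% aged 65 or over in the national audit figure and no younger patient is frail: 0.553 × 0.20 = 0.11.
- p = 0.30: z = 0.524, φ = 0.348, so 0.1209/0.210 = 0.58.

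The 1–9 score is itself coarse, so it does not keep everything either. Take the level proportions assumed in the simulation (0.15, 0.25, 0.40, 0.08, 0.05, 0.04, 0.02, 0.007, 0.003). With optimal scores the nine levels keep Σ[φ(lower cut) − φ(upper cut)]²/p_k = 0.92. With midranks, the squared correlation with the trait is 0.89. Against the rank-based figure the split keeps 0.49/0.89 = 0.55, still little more than half.

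**The case against.** The strongest reply has four parts.

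- **The 1–9 wording is a slip.** The range is loosely attached to a list of six markers, and nobody may intend to test CFS against itself. That may be so. But CFS is on the list under either reading, so the sentence as it stands includes the self-comparison.
- **Comparing other markers across CFS groups is ordinary validation.** This stands. Nothing in the article makes metabolites, psoas index, MUST, AMT or routine bloods inputs to CFS, and the contrast serves the part of the primary aim about identifying frailty.
- **Mortality is already analysed.** This also stands. CFS and the blood panel are both listed markers, and both enter the planned regression. The article does not spell out a model with CFS plus panel or name the ROC target, but a condensed article may leave such detail to the full protocol or analysis plan.
- **The cut at 4 is prespecified and cited, and the study is exploratory.** True, and this supports keeping the cut for description. It does not recover the information lost.

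Two stronger readings are tempting. A reader might infer that a panel assessed against CFS can never outperform it, so that the primary aim is capped by design. That holds only if the panel relates to death solely through CFS. If both are noisy measures of a latent frailty (assumed correlations with it 0.70 for CFS and 0.857 for the panel, 12% mortality), simulated AUCs for death are 0.687 for CFS and 0.727 for the panel. Moreover, the 12 named target metabolites come from earlier research in another cohort, and the article does not say that CFS bins select the panel.

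A reader might also infer that propensity score matching must be dropped because it discards patients. The article gives no matching ratio or covariate list, and regression is planned beside it, so this would be a preference.

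**Conclusion.** The point holds in a limited form. Comparing CFS between CFS groups is significant by construction (AUC 1.0; p about 4e-14 at 24 versus 96). The other between-group contrasts are valid as agreement with CFS, but they carry no evidence of improvement over it. The split at 4 keeps about 49% of the information in the underlying trait at 20% frail, with a range of 36% to 58% for 11% to 30% frail. These percentages rest on an assumed normal trait and assumed prevalence; that ordering is lost does not. The documents do not support the view that the primary aim is unattainable, because the mortality regression and ROC judge CFS and the panel on an outcome that does not depend on CFS.

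**What to change.** 1. Exclude CFS from the markers tested between CFS groups, and describe the remaining frail/non-frail contrasts as agreement with CFS.
2. Make the main metabolite-frailty analysis use CFS as an ordinal 1–9 variable on all patients, by rank correlation or regression with a CFS trend term. Keep the split at 4 for description and for the aim of identifying frailty.
3. Base any claim that the panel improves on CFS on the planned 30- and 90-day mortality analysis, reporting CFS alone, panel alone and CFS plus panel.

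The cost is analysis wording only, since all the data are already being collected. Ordinal results are slightly less simple to present than two groups. Item 3 should be reported with its limits. At an assumed 8–20% mortality, 120 patients give about 10 to 24 deaths. In the simulation with about 9 deaths, the likelihood-ratio test for adding the panel to CFS had about 57% power even for the strong effect above, so intervals matter more than p-values there.

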## Methods/ designs

### Patient recruitment

A prospective single centred observational study will be conducted in a National Health Service hospital that has an acute emergency surgical service. All consecutive emergency laparotomy (EmLAP) patients ≥ 40 years of age that undergo EmLAP will be screened and recruited. For patients who were deemed to have a lack of capacity to consent, their next of kin or welfare attorney will be approached to obtain written consent for the study pre-operatively. When the participant regains capacity, they will be approached to re-obtain consent to continue participation. Patients who do not regain capacity, the consent from next of kin or welfare attorney will continue. All recruited patients will be followed up for 90 days. The data collected after gaining consent and up to 90 days follow up are summarised in Fig. 1. Participant’s details will be pseudo-anonymised with a study ID.

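### Student's t-test and classical ANOVA pool the variances although the frail and non-frail groups will probably differ in size; naming Welch's versions is a cheap, minor improvement to the unadjusted comparisons

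*Protocol article*

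**What the plan says.** In the protocol article, the Statistical analysis section defines the main contrast: "The frailty markers (score 1–9) will be compared between groups of frail (CFS ≥ 4) and non-frail (CFS ≤ 3". For continuous variables it selects the test by distributional shape: "All normally distributed continuous variables will be assessed with Student’s T-test or the ANOVA test", and for the others "the rank based Kruskal- Wallis non-parametric test will be used to determine the statistical significance between the different groups". It mentions neither a variance check nor an unequal-variance version. The threshold is stated once: "A p-value of < 0.05 is considered statistically significant".

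The metabolomics paragraph of the same section takes a different route. After normalisation, frail and non-frail groups are compared "using the Kruskal-Wallis t-test or Mann Whitney test and subsequently in a regression model and propensity score matching", with a linear mixed model for changes over time. The association of frailty markers with mortality is analysed by adjusted regression and ROC curves.

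On group sizes, the Sample size section sets a target of 150 with 20% anticipated loss and no formal calculation. The only prevalence it cites is that "20% of older patients undergoing laparotomy had frailty pre- EmLAP", taken from an external study. The present cohort is wider: "All consecutive emergency laparotomy (EmLAP) patients ≥ 40 years of age".

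**The concern.** Student's t-test and classical ANOVA estimate one common variance. When the groups are of equal size this does little harm. When one group is much smaller, the pooled variance is dominated by the larger group. If the smaller group is the more variable, the standard error is too small and the test rejects too often even when the means are equal. If the smaller group is the less variable, the standard error is too large and real differences are missed.

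Because the article chooses the test on normality alone, a variable can pass the normality criterion and still be compared with a test whose error rate depends on an unexamined variance ratio. What is at stake is the reading of the unadjusted frail versus non-frail comparisons of roughly normal variables at p < 0.05.

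**Working it through.** **Inputs from the article.** Target 150; 20% loss, so 150 × 0.8 = 120 evaluable patients; level 0.05 (taken as two-sided, since the article does not say). The 20% frailty figure gives 0.2 × 120 = 24 frail and 96 non-frail, or 30 and 120 without loss.

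**Assumed inputs.** That the 20% applies to this cohort (varied to 30%, 40% and 50%), and the ratio r of the frail to the non-frail SD. The article gives no SDs, so r is varied from 0.67 to 2.

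**The plan's own figure.** The article states no error rate beyond p < 0.05, so there is nothing further to reproduce. With r = 1, simulation of 24 v 96 gives 4.9% for Student's test, as intended.

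**Large-sample formula.** With n1 frail, n2 non-frail and the non-frail SD set to 1:

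- variance used by Student's test: V_S = [((n1 − 1)r² + (n2 − 1)) / (n1 + n2 − 2)] × (1/n1 + 1/n2)
- true variance of the difference in means: V = r²/n1 + 1/n2
- type I error ≈ 2 × [1 − Φ(1.96 × √(V_S/V))]

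**24 v 96, r = 1.5.** V_S = (23 × 2.25 + 95)/118 × (1/24 + 1/96) = 1.2436 × 0.05208 = 0.0648. V = 2.25/24 + 1/96 = 0.1042. V_S/V = 0.622, and 1.96 × √0.622 = 1.546, which gives 12.2%.

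**24 v 96, r = 2.** V_S = (23 × 4 + 95)/118 × 0.05208 = 0.0825. V = 4/24 + 1/96 = 0.1771. V_S/V = 0.466, and 1.96 × √0.466 = 1.338, which gives 18.1%.

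**Simulation.** Normal data, equal means, 40,000 runs per setting; percentage of p-values below 0.05:

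| Split (frail share) | r | Student | Welch |
|---|---|---|---|
| 24:96 (20%) | 0.67 | 1.3 | 4.9 |
| 24:96 (20%) | 1.25 | 8.6 | 5.0 |
| 24:96 (20%) | 1.5 | 12.4 | 5.0 |
| 24:96 (20%) | 2 | 18.2 | 5.2 |
| 45:105 (30%) | 1.5 | 9.5 | 5.1 |
| 45:105 (30%) | 2 | 12.4 | 5.0 |
| 60:90 (40%) | 1.5 | 6.8 | 4.9 |
| 60:90 (40%) | 2 | 8.7 | 5.2 |
| 75:75 (50%) | 2 | 4.9 | 4.9 |

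Formula and simulation agree. A separate run of 20,000 simulations gave 1.5% for Student's test at r = 0.67, against 1.3% here; the difference does not matter. By the formula, the error at a 1:4 split reaches 10% at r = 1.34 and 20% at r of about 2.2.

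**Cost of Welch when r = 1.** At 24 v 96 and a true difference of 0.65 SD, simulated power is 80.4% for Student's test and 78.9% for Welch's. At 0.5 SD it is 58.5% and 56.7%. The loss is at most about 2 percentage points.

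**The case against.** The strongest objection is that nothing in the article shows the frail group to be more variable. A reader might infer greater spread from the grouping itself, since frail pools six CFS levels and non-frail only three. That does not carry the point, for two reasons. First, a marker that rises or falls steadily with CFS also differs in mean between the groups, so rejecting is then correct. Second, the mechanism is too weak. Take CFS uniform within each group, 20% frail, and a marker linear in CFS with constant residual variance. The within-group CFS variances are 35/12 = 2.917 and 8/12 = 0.667. The total CFS variance is 0.2 × 2.917 + 0.8 × 0.667 + 0.16 × 4.5² = 4.357. At a marker-CFS correlation of 0.5 the residual variance is 4.357 × (1/0.25 − 1) = 13.07, and the SD ratio is √(15.99/13.74) = 1.08. Correlations from 0.2 to 0.6 give only 1.01 to 1.13. This stands: ratios of 1.5 to 2 are assumptions.

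The 1:4 split is also inferred. The 20% comes from older patients elsewhere and is not stated as the expected share here. This stands too, and is why 30% and 40% are shown.

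A reader might further infer that the rank tests share the problem to the same degree, or that metabolites could enter the panel through Student's test. The article supports neither. Under the same assumptions Mann-Whitney rejects in about 8 to 11% of cases, a smaller excess. It is a valid test of equal distributions, and the article does not say that a mean is the target. Metabolites go first to rank tests and then to adjusted regression and propensity score matching, and no unadjusted p-value is made the rule for panel entry.

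Finally, the study is exploratory, and a condensed article may leave test details to the full plan. That lowers the weight of the point. It does not remove it, because the article names the pooled tests and does not leave the choice open.

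**Conclusion.** The point holds as a minor one. For normally distributed continuous variables the article fixes tests whose error rate depends on equal variances, in groups that are probably unequal in size. Given a 20% frail share and an assumed SD ratio of 1.5 to 2, the type I error is about 12 to 18%. It falls to about 9 to 13% at 30% frail and 7 to 9% at 40% frail, and is nominal at equal group sizes. In the other direction the test becomes conservative. No size can be claimed unconditionally, because the article gives no SDs and no expected frail share for this cohort. The effect is confined to the unadjusted comparisons of normally distributed continuous variables. It does not reach the rank tests named for metabolites or the adjusted mortality analysis, which serves the primary aim.

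**What to change.** In the Statistical analysis section, replace Student's t-test and ANOVA for normally distributed continuous variables with Welch's t-test and Welch's ANOVA, used by default and without a preliminary variance test. Optionally, state that linear regressions of markers on frailty group will use heteroscedasticity-robust standard errors, since ordinary standard errors there make the same equal-variance assumption. No change to the Mann-Whitney or Kruskal-Wallis tests is needed.

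The cost is a change of wording, and these methods are standard in statistical software. The only statistical price is the loss of about 2 percentage points of power if the variances are in fact equal.
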